**Table 6.4.1.6: irRC Definitions**

| Index Lesion Definition | Non-Index Lesion Definition | New Measurable Lesions | New Unmeasurable Lesion | % Change in Tumor Burden (including measurable new lesions when present) | Overall irRC Response |
|---------------------------------------|-------------------------------------------|--------------------------------------|---------------------------------------|----------------------------------------------------------------------------------------|-------------------------------------|
| Complete Response       | Complete Response           | No                     | No                      | -100%                                                                    | irCR                  |
| Partial Response        | Any                         | Any                    | Any                     | ≥ -50%                                                                   | irPR                  |
| Response                |                                           |                                      |                                       | < -50% to < +25%                                                   | irSD                  |

Table 6.4.1.6: *irRC Definitions*

| Index Lesion Definition | Non-Index Lesion Definition | New Measurable Lesions | New Unmeasurable Lesion | % Change in Tumor Burden
(including measurable new lesions when present) | Overall irRC Response |
|--------------------------------|------------------------------------|-------------------------------|--------------------------------|-------------------------------------------------------------------------------------|------------------------------|
|                                |                                    |                               |                                | $\geq +25\%$                                                                        | irPD                  |
| Stable Disease          | Any                         | Any                    | Any                     | $< -50\%$ to $< +25\%$                                                              | irSD                  |
| Stable Disease          | Any                         | Any                    | Any                     | $< -50\%$ to $< +25\%$                                                              | irSD                  |
|                                |                                    |                               |                                | $\geq +25\%$                                                                        | irPD                  |
| Progressive Disease     | Any                         | Any                    | Any                     | $\geq +25\%$                                                                        | irPD                  |

#### 6.4.3.4 *Derived Parameters When Using irRC Criteria*

##### *Immune Related Best Overall Response Using irRC (irBOR)*

irBOR is the best irRC overall response over the study as a whole, recorded between the date of first dose until the last TA prior to subsequent therapy (including tumor resection surgery but excluding local palliative radiotherapy for painful bone lesions) for the individual subject in the study. For the assessment of irBOR, all available assessments per subject are considered. irCR or irPR determinations included in the irBOR assessment must be confirmed by a second (confirmatory) evaluation meeting the criteria for response and performed no less than 4 weeks after the criteria for response are first met.

irBOR assessment of irSD requires an overall response of irSD (or unconfirmed irPR or irCR), in the absence of irBOR of irCR, irPR or irPD.

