Across the 3 groups in MDX010-20 and the pooled 3 mg/kg group from the Phase 2 studies, approximately 20% to 30% of subjects died during the induction phase. Most (> 90%) of the deaths were due to disease progression or other causes considered unrelated to study drug. In MDX010-20, treatment-related deaths (defined as a treatment-related AE with an outcome of death, reported at any time during the study) were reported in 4 subjects (3.1%), 8 subjects (2.1%), and 2 (1.5%) subjects in the ipilimumab monotherapy, ipilimumab plus gp100, and gp100 monotherapy groups, respectively. Of the 12 treatment-related deaths in the 2 ipilimumab-containing groups, 7 were associated with an irAE (GI perforation [4], colitis [1], liver failure [1], and Guillain-Barré Syndrome [1]). In addition, 1 subject in the ipilimumab plus gp100 group of MDX010-20 had a Grade 4 skin irAE (Stevens Johnson syndrome/toxic epidermal necrolysis/Lyell's syndrome), but died due to a treatment-related acute respiratory distress syndrome, which is not considered to be an irAE. In the pooled group from the Phase 2 studies, 2 subjects (1.8%) experienced treatment-related deaths, 1 of which was associated with an irAE (GI perforation).

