#### ***Non-Measurable Lesions:***

- Non-measurable lesions at baseline are all other lesions. These include small lesions (either or both diameter(s)  $<1.0$  cm), bone lesions, leptomeningeal disease, ascites, pleural or pericardial effusions, inflammatory breast disease, lymphangitis cutis/pulmonis, or cystic lesions.

- Ideally, the same method of assessment and the same technique should be used to characterize each identified and reported lesion at baseline and during follow-up. The reader will determine the technical adequacy should the technique/modality change.
- Superficial and palpable-only lesions will be non-measurable for the radiologic portion of the independent review. These lesions will be considered as non-measurable during the IRC assessment unless there are no suitable radiographically measurable lesions. For this clinical assessment, cutaneous lesions should be photographed by a standard technique at each assessment point to document the clinical response. Copies of other imaging assessments, such as chest x-ray or ultrasound, which are not considered measurable for the radiologic assessment but measurable for the clinical assessment, will be kept centrally to document evidence of clinical response.

All measurable and non-measurable lesions should be assessed at Screening and at the defined TA time points (see Table 6.1). Extra assessments may be performed, as clinically indicated, if there is a suspicion of progression.

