#### **Calculation of Sum of Product of Diameters (SPD)**

SPD is an estimation of tumor burden. The 2 greatest perpendicular diameters are used to estimate the size of each tumor lesion. The SPD is calculated as the sum of the product of the diameters for index tumor lesions. Several variations of the SPD are identified for the purpose of classification of tumor responses.

SPD at Baseline: The sum of the product of the diameters for all index lesions identified at baseline prior to treatment on Day 1.

SPD at TA: For every on-study TA collected per protocol Section 6.1 or as clinically indicated, the SPD at TA will be calculated using tumor imaging scans.

SPD at Nadir: For tumors that are assessed more than one time after baseline, the lowest value of the SPD (SPD Baseline or SPD at TA) is used to classify subsequent TAs for each subject.

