***Definition of Overall Response Using irRC Will Be Based on the Following Criteria:***

- Immune-related Complete Response (irCR): Complete disappearance of all tumor lesions (index and non-index together with no new measurable/unmeasurable lesions) for at least 4 weeks from the date of documentation of irCR.
- Immune-related Partial Response (irPR): The sum of the products of the 2 largest perpendicular diameters of all index lesions is measured and captured as the SPD baseline. At each subsequent TA, the sum of the products of the 2 largest perpendicular diameters of all index lesions and of new measurable lesions are added together to provide the Immune Response Sum of the Product of the Diameters (irSPD). A decrease, relative to baseline of the irSPD of 50% or greater is considered an irPR. It must be confirmed no less than 4 weeks from the first irPR.
- Immune-related Stable Disease (irSD): irSD is defined as the failure to meet criteria for immune complete response or immune partial response, in the absence of progressive disease.
- Immune-related Progressive Disease (irPD): Unless the subject is rapidly deteriorating, a confirmatory scan not less than 4 weeks since the prior scan should be performed to confirm PD. Any of the following will constitute progressive disease:
  - At least 25% increase in the SPD of all index lesions over nadir SPD calculated for these lesions.
  - At least a 25% increase in the SPD of all index lesions and new measurable lesions (irSPD) over the nadir SPD calculated for the index lesions.

Immune-related clinical activity (irCR, irPR or irSD) relative to baseline can be recorded at any time, including after confirmed irPD, provided that the patient has not received alternative non-ipilimumab anticancer therapy.

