### 8.3.2 Secondary Endpoints

#### 8.3.2.1 Secondary Efficacy Endpoints based on immune-related Response Criteria

Tumor assessment, using the immune-related response criteria (ir-RC), is made by the investigator.

Immune-related Disease Control Rate (irDCR) is the proportion of treated subjects with an ir-BOR of confirmed irCR, confirmed irPR or irSD.

Immune-related Objective Response Rate (irORR) is the proportion of treated subjects with a irBOR of confirmed irCR or confirmed irPR.

Immune-related Time to Response (irTTR) is defined as the time from first dosing date until the measurement criteria are first met for overall response of irPR or irCR (whichever status comes first, and provided it is subsequently confirmed).

Immune-related Duration of Response (irDoR) for the subjects whose irBOR is irCR or irPR will be defined as the time between the date of response of confirmed irCR or confirmed irPR (whichever occurs first) and the date of irPD or death (whichever occurs first). The onset of a confirmed irCR or irPR is determined by the initial assessment of response, not by the confirmatory assessment. Note that if an assessment of irPR occurs before confirmation of irCR, the duration of immune-related response endpoint will not begin at the time that the irBOR of irCR is shown but rather at the earlier time-point showing irPR. For subjects who remain alive and have not progressed following response, irDoR will be censored on the date of last evaluable TA.

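### irSD has no earliest qualifying date, so a patient whose unscheduled early scan reads irSD and who dies before Week 12 counts as disease control in irDCR

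*Combined protocol and SAP*

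**What the plan says.** Section 6.4.3.3 defines stable disease by exclusion: "irSD is defined as the failure to meet criteria for immune complete response or immune partial response, in the absence of progressive disease". It gives no minimum duration, and it adds that clinical activity, irSD included, "relative to baseline can be recorded at any time, including after confirmed irPD".

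Section 6.4.3.4 requires irCR and irPR to be confirmed at least 4 weeks later. For stable disease it says only that "irBOR assessment of irSD requires an overall response of irSD (or unconfirmed irPR or irCR"; the sentence then closes its bracket and excludes patients whose irBOR is irCR, irPR or irPD. The same section states: "For the assessment of irBOR, all available assessments per subject are considered".

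Unscheduled scans are permitted and measured. Under non-measurable lesions in section 6.4.3.2: "Extra assessments may be performed, as clinically indicated, if there is a suspicion of progression". Under the SPD calculation, the SPD is derived "For every on-study TA collected per protocol Section 6.1 or as clinically indicated".

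In section 8.3.2.1, irDCR "is the proportion of treated subjects with an ir-BOR of confirmed irCR, confirmed irPR or irSD". In section 8.3.2.2, death without reported progression is a progression event for irPFS. No matching rule exists for irBOR or irDCR.

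The first scheduled post-baseline tumor assessment is Week 12 in the synopsis, section 4.1.2 and the flow chart in section 6.1, although these places disagree about later visits.

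**The concern.** Disease control is meant to capture durable stabilisation: section 1.3.6.2 justifies DCR for ipilimumab by long-lasting stable disease or slow decline. As defined, one scan at any time after first dose is enough. On the scheduled path this does no harm, because the first scan is at Week 12. An optional early scan changes the result. It is done because progression is suspected, yet if growth is below the threshold it can only help the patient count as controlled.

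irDCR then depends partly on who was scanned early, and the same patient can be an irPFS event and a disease-control success. With at most 19 patients, one or two such cases visibly move the reported rate.

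**Working it through.** The plan gives no target irDCR, power or formal sample size, so there is no stated figure to reproduce. I applied the rules to a case and then sized the effect.

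**The case.** A patient is scanned at Week 5 for suspected progression. The irSPD is 20% above nadir, with no response. The patient dies at Week 9 without another scan.

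1. Growth is below the 25% threshold, so the overall response is irSD (section 6.4.3.3 and Table 6.4.1.6).
2. The scan is an available assessment, so it enters irBOR. No other irBOR category applies, so irBOR is irSD.
3. irBOR of irSD counts in irDCR.
4. The death at Week 9 is an irPFS event.
5. The same patient without the Week 5 scan has no irSD on record. This patient stays in the denominator of treated subjects and does not count as controlled.

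**Effect per patient.** 1/19 = 5.3 points; 1/6 = 16.7 points (the synopsis gives 6 to 19 patients).

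**Effect on the estimate**, using the exact two-sided 95% intervals of section 8.4.3. The true count of 6 is an assumption for illustration.

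| Count | irDCR (95% CI) |
|---|---|
| 6/19, none misclassified | 31.6% (12.6-56.6) |
| 7/19, one misclassified | 36.8% (16.3-61.6) |
| 8/19, two misclassified | 42.1% (20.3-66.5) |

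**Expected inflation.** Let d be the probability of death before Week 12, and s the share of those deaths with an early scan reading irSD and no later scan. Expected inflation is 100 × d × s points. The chance of at least one such patient among 19 is 1 − (1 − d × s)^19.

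Neither input is given for this trial. For d, section 1.3.6.3 reports that "approximately 20% to 30% of subjects died during the induction phase" in earlier studies. I take that as the upper end and assume 5-10% as a lower range, since section 4.2.1 requires life expectancy above 16 weeks and ECOG 0-1. For s, I assume 10%, 25% and 50%. Cells show points of inflation, then the chance of at least one case in 19.

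| d | s = 10% | s = 25% | s = 50% |
|---|---|---|---|
| 5% | 0.5; 9% | 1.25; 21% | 2.5; 38% |
| 10% | 1.0; 17% | 2.5; 38% | 5.0; 62% |
| 20% | 2.0; 32% | 5.0; 62% | 10.0; 87% |
| 30% | 3.0; 44% | 7.5; 77% | 15.0; 95% |

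**The case against.** The strongest reply is that the gap is narrow. Section 1.3.6.2 says tumor response should be assessed only after induction is complete, and every schedule puts the first post-baseline scan at Week 12. In the ordinary course irSD already means about 12 weeks without progression. That stands as a limit on frequency. It does not close the gap, because the sentence is background on ipilimumab, sections 6.4 and 8.3 never apply it, and section 6.4 expressly allows and measures unscheduled scans.

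A reader might infer that every patient scanned early for suspected progression who then dies is scored as controlled. The documents do not support that. At 25% growth or more over nadir the response is irPD, with confirmation waived in rapid deterioration, and scans prompted by suspected progression are plausibly more likely to cross that line.

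A reader might also take the 20-30% induction deaths as the rate expected here and infer a rise of 10 to 15 points. That rate comes from earlier studies and includes a gp100-only arm. This trial requires life expectancy above 16 weeks and ECOG 0-1, admits untreated patients and excludes active brain metastases. The 50% share needed for that figure has no source in the documents.

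Finally, the synopsis says the study may be terminated if no irDCR is seen. One early irSD would turn 0/19 (0.0-17.6%) into 1/19 (5.3%, 0.1-26.0%), and it is tempting to say this disables a stopping rule. The sentence is discretionary, has no timepoint, and is absent from sections 5.2.2 and 8.1. Section 8.5 plans no interim efficacy analysis. There is no binding rule to disable.

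**Conclusion.** The point holds for patients whose early scan reads irSD and who die before Week 12. For them the stated rules give disease control, and relative to a Week 12 requirement the error can only raise irDCR. The size per patient is fixed: 5.3 points at N=19 and 16.7 at N=6. The number of such patients is unknown. The 0.5 to 15 point range rests wholly on assumed early deaths of 5-30% and an assumed 10-50% of those with an early irSD scan; its upper end should not be read as an expectation.

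The consequence is limited. Section 8.4.3 treats the secondary efficacy endpoints as explorative, irORR is unaffected because it needs confirmed responses, and early deaths still appear in irPFS and OS. The MTD and safety conclusions do not change. The definition should be corrected because the bias has a known direction and the remedy uses scans already scheduled.

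**What to change.** In sections 6.4.3.4 and 8.3.2.1, state the following:

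- irSD, including an unconfirmed irPR or irCR scored as irSD, counts for irBOR and irDCR only if documented at or after the scheduled Week 12 tumor assessment.
- The visit window for that assessment is given explicitly. The flow chart's ±3 days is headed Treatment Phase, and Week 12 falls under Follow-up with no stated window.
- Treated patients with no qualifying assessment, including those who die before Week 12, count as not controlled unless they already have a confirmed irCR or irPR.
- Earlier scans may still establish irPD or the onset of a response.

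Amend the sentence in section 6.4.3.4 that admits all assessments, and the one in section 6.4.3.3 that lets irSD be recorded at any time, so that they agree with this rule. Reconcile section 1.3.6.2, which places response assessment after induction, with the text allowing unscheduled scans.

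The cost is a short amendment to several linked passages and a slightly lower reported irDCR. No extra scans are needed.

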## 6.5 Pharmacokinetic Assessments

Cycle 1, Day 1 with the following time-points: pre-dose, 15 min, 30 min, 60 min, 90 min, 2 hr, 4 hr, 6 hr and 8 hr post-dose. For a detailed workplan of pharmacokinetic analyses see **Appendix B**.

## 6.6 Translational Research

For a detailed work plan of translational studies see Appendix A

## 7 ADVERSE EVENTS

### 7.1 Definitions

An Adverse Event (AE) is defined as any new untoward medical occurrence or worsening of a pre-existing medical condition in a patient or clinical investigation subject administered an investigational (medicinal) product and that does not necessarily have a causal relationship with this treatment. An AE can therefore be any unfavorable and unintended sign (including an abnormal laboratory finding, for example), symptom, or disease temporally associated with the use of investigational product, whether or not considered related to the investigational product.

#### 7.1.1 *Serious Adverse Events*

A serious AE (SAE) is any untoward medical occurrence that at any dose:

- results in death,
- is life-threatening (defined as an event in which the subject was at risk of death at the time of the event; it does not refer to an event which hypothetically might have caused death if it were more severe),
- requires inpatient hospitalization or causes prolongation of existing hospitalization (see note below for exceptions),
- results in persistent or significant disability/incapacity,
- is a congenital anomaly/birth defect ,
- is an important medical event (defined as a medical event(s) that may not be immediately life-threatening or result in death or hospitalization but, based upon appropriate medical and scientific judgment, may jeopardize the subject or may require intervention [e.g., medical, surgical] to prevent one of the other serious outcomes listed in the definition above.) Examples of such events include, but are not limited to, intensive treatment in an emergency room or at home for allergic bronchospasm; blood dyscrasias or convulsions that do not result in hospitalization).

Suspected transmission of an infectious agent (e.g., any organism, virus or infectious particle, pathogenic or non-pathogenic) via the study drug is an SAE and must be reported accordingly.

Although overdose and cancer are not always serious by regulatory definition, these events should be reported on an SAE form and sent to Fondazione NIBIT/CRO that will forward to BMS in an expedited manner.

All pregnancies, regardless of outcome, must be reported to the sponsor on a Pregnancy Surveillance Form, not an SAE form (see Section 7.7).

NOTE:

The following hospitalizations are not considered SAEs in Fondazione NIBIT clinical studies:

- a visit to the emergency room or other hospital department < 24 hours, that does not result in admission (unless considered "important medical event" or event life threatening),
- elective surgery, planned prior to signing consent,
- admissions as per protocol for a planned medical/surgical procedure,
- routine health assessment requiring admission for baseline/trending of health status (e.g., routine colonoscopy),
- medical/surgical admission for purpose other than remedying ill health state and was planned prior to entry into the study. Appropriate documentation is required in these cases,
- admission encountered for another life circumstance that carries no bearing on health status and requires no medical/surgical intervention (e.g., lack of housing, economic inadequacy, care-giver respite, family circumstances, administrative),
- Death due to disease progression.

### **7.1.2 Non serious Adverse Events**

All AEs that are not classified as serious.

## **7.2 Dose-limiting Toxicities**

Dose-limiting toxicities are defined in Section 5.3.

All presumed DLTs (as defined in Section 5.3) must be recorded immediately, i.e., within a maximum of 24 hours after becoming aware of the event, in the eCRF irrespective of seriousness and the event must be specified as a DLT. In addition, serious DLTs must be reported in an expedited manner according to the procedure for SAEs, as outlined above. Unless an NCI-CTCAE Grade 4 hematologic or a Grade 3/4 non-hematologic toxicity that occurs during the DLT observation period is clearly due to a non-drug cause, the Investigator should consider all AEs seen during the DLT observation period (from Day 1 to Day 21 of Cycle 1) to be at least possibly related to the trial treatment. In addition, the methods described in Section 6.3.5 and 7.4 should be used to assess all AEs throughout the trial until after completion of the SFU Visit(s).

Section 4.1.3 outlines the responsibilities of the SMC with respect to DLTs.

### **7.3 Assignment of Adverse Event Intensity and Relationship to Study Drug**

All adverse events, including those that are serious, will be graded according to the National Cancer CTCAE version 4.

The following categories and definitions of causal relationship to study drug as determined by a physician should be used for all NIBIT clinical study AEs:

- Related: There is a reasonable causal relationship to study drug administration and the AE
- Not related: There is not a reasonable causal relationship to study drug administration and the AE.

The expression "reasonable causal relationship" is meant to convey in general that there are facts (e.g., evidence such as de-challenge/re-challenge) or other arguments to suggest a positive causal relationship.

